## Abstract

**Background:**

Tension-type headache (TTH) is the most common headache disorder. Current treatments for TTH have been reported to be associated with insufficient long-term benefits and unwanted adverse events (AEs). The Chinese herbal formula Xuefu Zhuyu (XFZY) has been utilized in TTH treatment, but the evidence supporting its efficacy remains unclear. This study will evaluate the efficacy and safety of XFZY for TTH.

**Methods:**

This multicenter, double-blind, randomized, placebo-controlled trial will be undertaken in China. A total of 174 eligible participants will be randomly assigned to either an XFZY group or a placebo group (20 ml each dose, three times daily for 4 weeks) at a ratio of 1 : 1. The primary outcome is the change in mean headache intensity measured by a 10 cm visual analogue scale (VAS). Secondary outcomes include the area-under-the headache curve (AUC), headache frequency, rescue medication use, *qi-stagnation and blood-stasis* pattern measurement, quality of life measured by the EuroQol-5-Dimensions-5-Level (EQ-5D-5L), global evaluation of medication, and health economic indexes. *Discussion*. The results of the study are expected to provide evidence of high methodological and reporting quality on the efficacy and safety of XFZY for TTH. This trail is registered with ChiCTR1900026716 (registered on 19 October, 2019).

## 1. Introduction

Tension-type headache (TTH) is the most prevalent headache disorder [1, 2] and the second most common disease in the 2010 Global Burden of Disease Survey [3, 4]. It has a lifetime prevalence ranging from 30% to 78% [5]. In China, the years lived with disability (YLDS) for TTH are second only to migraine among headache disorders [2]. This has immense social and economic costs. Overall absence rates for subjects with frequent TTH are on the rise, despite not increasing for migraines [6]. Hence, it is one of the most costly disorders to society [7]. In order to improve Chinese citizens' quality of life, treating TTH should be a national priority [2].

Simple analgesics and nonsteroidal anti-inflammatory drugs (NSAIDS) are recommended for episodic TTH (ETTH) by the European Federation of Neurological Societies (EFNS) [8] and the British Association for the Study of Headache (BASH) [9]. They have been shown to be to be effective for ETTH [10–12] but not for chronic TTH (CTTH). As headache frequency increases, so does the risk of medication overuse, especially in CTTH. The tricyclic antidepressant amitriptyline is the primary choice for the prophylactic treatment of CTTH [8]. However, the effect of these drugs is not satisfactory because of insufficient effect or side effects [13, 14]. The combination of caffeine with simple analgesics is more effective for the treatment of ETTH than simple analgesics alone, but at the cost of an increased frequency of side effects [15, 16]. Hence, combination analgesics containing caffeine are treated as the second choice for ETTH by EFNS guideline [8]. Opioids should not be used because of drug resistance, dependence, and toxicity [8]. Furthermore, the use of these drugs also increases the risk of forming medication-overuse headache (MOH) [17]. Other treatments have also been applied in clinic, including Chinese medicine (CM) therapies, cognitive behavioral therapy, physical therapy, stress management, and acupuncture, but the evidence for these treatments is limited or inconsistent [18, 19]. Therefore, more research is needed to explore new medications.

Chinese herbal medicine (CHM) has a long history in China and other regions of Asia. It is the main form of CM and could provide further options for headache treatment. The Chinese herbal formula Xuefu Zhuyu (XFZY) is the representative, classical CHM prescription for the treatment of headache. It has been widely used in the treatment of headache with *Qi-stagnation and Blood-stasis* pattern (QBS) (also called Zheng in CM). XFZY oral liquid is a patented product, which has been approved by the China Food and Drug Administration in 2002 (Ref No. Z10950063) [20]. It is an improved dosage form of XFZY decoction [21], which strictly follows the original prescription and dosage of XFZY decoction. Hence, they have the same function in promoting and activating the flow of *qi* and *blood* to treat QBS. This treatment has been utilized since the Qing Dynasty. XFZY consists of Bupleuri Radix (chaihu), Angelicae Sinensis Radix (danggui), Rehmanniae Radix (shengdihuang), Paeoniae Radix Rubra (chishao), Carthami Flos (honghua), Persicae Semen (taoren), Aurantii Fruxtus (zhiqiao), Glycyrrhizae Radix et Rhizoma (gancao), Chuangxiong Rhizoma (chuanxiong), Achyranthis Bidentatae Radix (niuxi), and Platycodonis Radix (jiegeng). A document to describe the components of the XFZY and pharmaceutical production processes were offered in supplementary file S1. Experimental studies have revealed that XFZY has an anticoagulating effect and improves microcirculation by reducing blood viscosity [22–25]. Clinical studies have shown that XFZY is effective in treating headache disorders, especially in migraine [26, 27], but the evidence of XFZY for TTH is absent. Therefore, the aim of this trial is to investigate whether the efficacy and safety of XFZY for TTH patients with QBS is superior to placebo.

## 2. Methods

### 2.1. Study Design and Setting

This is a multicenter, double-blinded, randomized, placebo-controlled trial that will be conducted in six hospitals located in different regions of China. The screening condition of the center is whether the hospital is a state clinical research base or a clinical trial institution and can complete the observation of at least 20 patients. Six centers are listed below: (1) Affiliated Hospital of Liaoning University of Traditional Chinese Medicine; (2) Second Affiliated Hospital of Guangzhou University of Chinese medicine; (3) Second Hospital Affiliated to Liaoning University Traditional Chinese Medicine; (4) First Hospital of China Medical University; (5) Shenyang 10th people's Hospital; and (6) Affiliated Hospital of Inner Mongolia University for the Nationalities. Eligible participants will be randomly assigned to either an experimental group or a placebo group at a ratio of 1 : 1 (Figure 1). The trial's protocol reporting follows the Standard Protocol Items for Clinical Trials with Traditional Chinese Medicine (SPIRIT-TCM) (Supplementary file S2) [28].

### 2.2. Participants

We will recruit potential eligible participants via newspaper advertisements, notice boards, and outpatient visits, and also pay attention to whether the recruitment and enrollment progress reached the target sample size. Patients who meet the inclusion criteria and sign informed consent forms will enter the screening period; otherwise, they will be excluded before randomization.

Patients in each center will be diagnosed and differentiated by a senior neurologist and will be observed by a neurologist at a specialist clinic. TTH diagnostic criteria include (1) Western medicine diagnosis based on the criteria of the International Classification of Headache Diseases-3 (ICHD-3) published by the International Headache Society (IHS) in 2018 [5] and (2) pattern diagnosis according to a validated QBS diagnostic scale [29] (Table 1).

Eligibility criteria are as follows: (1) TTH must have occurred for at least 1 year, at least 2 days per month (unlimited frequency), and at least one TTH attack needs to have lasted over 4 hours; (2) a visual analogue scale (VAS) score ≥3 cm; (3) the first onset of TTH need to have happened before the age of 50 years; (4) aged 18–65 years; and (5) CM pattern differentiation is QBS.

Exclusion criteria are (1) concurrent migraine; (2) ailment diagnosed as secondary headache by computed tomography (CT) and transcranial Doppler (TCD) within the previous 6 months; (3) having serious primary diseases such as those of the cardiovascular, liver, kidney or hematopoietic system, and psychosis (schizophrenia, epilepsy, alcoholism, and anorexia) or major neuropsychiatric diseases; (4) labs showing increase in alanine aminotransferase (ALT) or aspartate aminotransferase (AST) over twice the upper limit of the normal range or an increase in creatinine over 1.5 times of the upper limit of the normal range; (5) suffering from other severe pain-inducing diseases, such as cancer; (6) patients with a Self-rating Anxiety Scale (SAS) greater than 59 or Self-rating Depression Scale (SDS) greater than 62; (7) potential allergy to XFZY; (8) women who are either pregnant, lactating, or planning to get pregnant; and (9) participating in other clinical trials within the previous month.

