### 2.4. Blinding

The investigators, participants, research assistants, and statisticians will be blinded to the allocated treatment. Both the XFZY and the matched placebo are manufactured by Jilin Aodong Yanbian Pharmaceutical Co., Ltd. (Dunhua, Jilin, China). The placebo is identical in color, size, dosage form, smell, and taste to XFZY. Both XFZY and the placebo will be labeled and packaged based on a randomization schedule from the clinical research department at Jilin Aodong Yanbian Pharmaceutical Co., Ltd., under the supervision of IBRCM. The blinding code will not be revealed until the end of the trial, unless a patient has a serious adverse event (SAE) or emergency which necessitates knowing what medications have been taken.

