#### 2.5.3. Rescue and Concomitant Treatment

Participants in both groups will be consistent in usage, dosage, and trial period. The painkiller (acetaminophen) will be allowed to relieve symptoms, if unbearable pain remains after taking the study drugs for two hours. During the treatment period, use of CM decoction, other CM products, acupuncture, massage, or cupping therapy with the CM function of moving *qi* and/or activating *blood* will be forbidden.

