### 2.6. Drug Compliance

The drug compliance is measured by the tablet count. The patients are asked to return the packaging from the drugs they have already taken at each follow-up visit, throughout the study period. The formula is based on the amount of medication taken divided by the total amount of medication to be taken, and ≥80% will be considered high compliance.

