### 2.8. Safety Assessment

Any adverse events (AEs) that occur during the study period will be reported to the research assistants, and the causality between AE and drug will be assessed according to the WHO Uppsala Monitoring Center System for Standardized Case Causality Assessment [34]. Laboratory examinations including the blood routine test, urine routine test, liver function, kidney function, coagulation function, and electrocardiogram will be performed at the baseline and the fourth week. Attention is paid to the abnormal changes of laboratory test results, they are recorded as an AE if they have clinical significance, and the causality with the study drug is assessed.

An independent Data and Safety Monitoring Committee (DSMC) will also evaluate the safety data which will be requested during the trial. Severe AEs (SAEs) or severe adverse reactions (SARs) are defined according to the International Council for Harmonization of Technical Requirements for Pharmaceuticals for Human Use (ICH) guidelines [35]. They must be reported to the DSMC, the GPHCM ethnics committee, and the research team within 24 h. AE or SAE details such as occurrence, severity, management, and causality to the intervention will be recorded on electric case report forms (eCRFs). In emergency situations, physicians will be consulted, and the blinding will be broken if necessary.

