## Figures and Tables

**Figure 1 fig1:**
[figure not shown]
Study flow chart.

**Table 1 tab1:** QBS diagnosis scale.

Symptoms/signs	Yes	No	Score
Pain	9	0	
Irritability/depression	16	0	
Distending pain	2	0	
Scurry pain	6	0	
Chest distress	0.5	0	
Lumps in body	7	0	
Petechia in the tongue	4	0	
Purplish tongue	1	0	
Unsmooth pulse	4	0	
Deep pulse	2	0	
Total score If ≥20 points, diagnosed as QBS			

Notes: pain includes stomachache, abdominal pain, low back pain, dysmenorrhea, breast pain, and limb pain. QBS: *Qi*-stagnation and Blood-stasis pattern.

**Table 2 tab2:** Outcome measures.

Domain	Measure	Time (weeks)
*Primary*		
Mean pain intensity of headache change	10 cm VAS with “none” and “very severe” at either end	0, 1, 2, 4, 8, 12
Secondary		
AUC	Calculated by the sum of the daily headache duration (hours) multiplied by the daily headache intensity in each observed period and, then, divided by the observation period	0, 1, 2, 4, 8, 12
Headache frequency	Defined as a ≥50% reduction by the number of days with a headache or attacks per evaluation period; headache hours for each observed period	0, 1, 2, 4, 8, 12
Headache hours	The total hours in each observed period	0, 1, 2, 4, 8, 12
Rescue medication use	Records the number of participants using the rescue medication and the total dosage per week	0, 1, 2, 4, 8, 12
QBS measurement	Evaluated by a qualified CM physician	0, 1, 2, 4, 8, 12
Quality of life	EQ-5D-5L	0, 4, 12
Global evaluation of medication	A simple verbal scale: very poor, poor, neutral, good, very good	4
Health economic indexes	Registration costs, laboratory tests, drugs (other than the experimental drug), hospital admission, transportation, average monthly income, costs incurred by family caregivers	0, 1, 2, 4

VAS: visual analogue scale, AUC: area-under-the-headache curve. EQ-5D-5L: EuroQol-5-Dimensions-5-Level.

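### The protocol calls XFZY anticoagulating, but neither its exclusion list nor its concomitant-treatment rule covers anticoagulant or antiplatelet drugs

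*Protocol article*

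**What the plan says.** The Introduction of the protocol article describes the pharmacology of the study drug: "Experimental studies have revealed that XFZY has an anticoagulating effect and improves microcirculation by reducing blood viscosity".

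Section 2.2 lists nine numbered exclusions. The one closest to this topic is exclusion (3), which removes patients "having serious primary diseases such as those of the cardiovascular, liver, kidney or hematopoietic system", together with certain psychiatric and neurological conditions. Exclusion (4) sets entry limits for ALT, AST and creatinine. Exclusion (7), potential allergy, is the only one that refers to XFZY itself.

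Section 2.5.3 allows acetaminophen as rescue. During treatment it forbids "use of CM decoction, other CM products, acupuncture, massage, or cupping therapy with the CM function of moving" qi and/or activating blood. It does not mention conventional drugs that act on clotting.

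Section 2.8 covers safety monitoring. Laboratory work including "liver function, kidney function, coagulation function, and electrocardiogram will be performed at the baseline and the fourth week", and for abnormal changes the rule is: "Attention is paid to the abnormal changes of laboratory test results, they are recorded as an AE if they have clinical significance".

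**The concern.** A trial that describes its drug as anticoagulating would be expected to say what happens to patients who already take an anticoagulant or antiplatelet drug, or who need to start one. If the two effects add up, such a patient carries a risk that the protocol's own background points to, and takes blinded study drug for 4 weeks with no stated rule. The stake is patient safety before first exposure. It is not the validity of the comparison: randomisation is stratified by center and blinded, and nothing here suggests that users of these drugs would fall unevenly between the arms.

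**Working it through.** The plan states no figure on this point, so the check is a side-by-side reading of the rules.

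1. **Stated effect.** The Introduction attributes anticoagulation and lower blood viscosity to XFZY. The source is experimental work. It reports no bleeding and no drug interaction.

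2. **Exclusions, section 2.2.** In order they concern: (1) migraine; (2) secondary headache; (3) serious organ disease, psychosis or major neuropsychiatric disease; (4) ALT, AST and creatinine; (5) other severe painful disease; (6) anxiety and depression scores; (7) allergy; (8) pregnancy, lactation or planned pregnancy; (9) other trials. Exclusions that name anticoagulant or antiplatelet use: 0 of 9. The list is numbered and ends at (9), so it reads as complete.

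3. **What exclusion (3) catches.** It excludes by disease, and the disease must be serious. Its wording is open-ended, so it can be applied broadly. Most people on these drugs probably take them for serious cardiovascular or blood disease and would be excluded. The patient left over takes one for a condition judged not serious, for example low-dose aspirin at an age within the 18 to 65 range. No stated criterion excludes that patient.

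4. **Concomitant treatment, section 2.5.3.** The ban is defined by CM function, and that function is the one the Introduction ascribes to XFZY. A CM product with that action is forbidden. A conventional drug that acts on clotting is not mentioned, so a participant may also start one during treatment.

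5. **Cover after dosing starts.**
   - Table 2 schedules assessments at weeks 1, 2 and 4. One of them, the pattern measurement, is "Evaluated by a qualified CM physician". The gaps during dosing are 7, 7 and 14 days.
   - Section 2.6 adds contact for compliance: "The patients are asked to return the packaging from the drugs they have already taken at each follow-up visit".
   - Section 2.8 provides AE reporting, an independent safety committee that evaluates safety data, and reporting of serious events to that committee, the ethics committee and the research team within 24 hours.
   - Section 2.4 allows unblinding: "The blinding code will not be revealed until the end of the trial, unless a patient has a serious adverse event (SAE) or emergency".
   - Coagulation is retested at week 4, that is 4 × 7 = 28 days after baseline. This is when treatment ends, so the result cannot guide dosing.

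Every item in step 5 works after first exposure. An eligibility line works before it, and none is stated.

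**The case against.** The strongest objection is that this is an omission from a condensed article. The Data Availability statement identifies a protocol, V1.0/20190920. Lists of prohibited drugs by class commonly sit in such a document and may do so here. This carries real weight for the concomitant-treatment line. It carries less for eligibility, because section 2.2 sets the criteria out as a numbered, finished list rather than a summary.

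A second objection is that the Introduction gives only a background sentence about experimental work on a product it says was approved in 2002. A reader might infer that the documents show a bleeding hazard with conventional drugs. They do not, so the point can only be precautionary.

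Third, the CM ban may be there to protect the efficacy comparison and not to prevent bleeding. That is a fair reading. It means section 2.5.3 is not a failed bleeding rule, but it leaves the gap where it is.

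Fourth, investigator judgement combined with monitoring is a defensible alternative to a blanket exclusion. This stands as to method, and it is why the fix leaves continuation of study drug to the investigator. The article does not, however, state even that rule for these drugs.

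A reader might also infer that nobody looks at the baseline coagulation result before randomisation. The documents do not support this. They give no coagulation threshold, but silence does not show that the result goes unread. Exclusion (4) requires liver enzymes and creatinine to be known before entry, and section 2.8 places coagulation in the same baseline panel as liver and kidney function.

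**Conclusion.** The point holds as a minor, precautionary one, worth considering. As written, a patient on an anticoagulant or antiplatelet drug for a condition not judged serious can be enrolled, and another participant can start such a drug during treatment, in a trial whose Introduction calls the study drug anticoagulating.

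Neither the bleeding risk nor the number of such patients among the planned 174 can be derived from the documents. The number may be zero, and any assumed share would be a guess. The conclusion rests on two assumptions: that the experimental effect could matter clinically, and that the rules in sections 2.2 and 2.5.3 are complete as stated. If the full protocol already deals with these drugs, the remaining issue is one of reporting only.

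A reader might infer a threat to the efficacy or safety comparison. Nothing in the documents supports that, and none is claimed.

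**What to change.** - **Section 2.2:** add exclusion (10), *current use of an anticoagulant or antiplatelet drug*.
- **Section 2.5.3:** add that such drugs should not be started during the 4-week treatment unless medically necessary. If one is necessary it is given, the investigator decides whether study drug continues, and the patient stays in follow-up and in the ITT analysis.

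If the full protocol already contains these rules, apply them and show them in the published lists.

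The cost is two lines by amendment and no new test. A few recruits may be lost (the number is not known from the documents and may be none), and the results would apply to a slightly narrower population.

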### 2.3. Randomization

A block randomization sequence stratified by centers is generated by SAS 9.2 (SAS Institute Inc., Cary, USA) and performed by the Institute of Basic Research in Clinical Medicine (IBRCM), China Academy of Chinese Medical Sciences, through an interactive web response system. When eligible patients who have signed informed consent forms are enrolled, an independent researcher will log into the system to obtain their allocation results. The randomization results will be kept confidential and maintained by IBRCM. All patients and researchers, including investigators, outcome assessors, statisticians, and other staff involved in the trial will be unaware of the grouping and treatment during the study period.

### 2.4. Blinding

The investigators, participants, research assistants, and statisticians will be blinded to the allocated treatment. Both the XFZY and the matched placebo are manufactured by Jilin Aodong Yanbian Pharmaceutical Co., Ltd. (Dunhua, Jilin, China). The placebo is identical in color, size, dosage form, smell, and taste to XFZY. Both XFZY and the placebo will be labeled and packaged based on a randomization schedule from the clinical research department at Jilin Aodong Yanbian Pharmaceutical Co., Ltd., under the supervision of IBRCM. The blinding code will not be revealed until the end of the trial, unless a patient has a serious adverse event (SAE) or emergency which necessitates knowing what medications have been taken.

### 2.5. Interventions

#### 2.5.1. Experimental Group

In the experimental group, participants will take 20 ml XFZY orally, 3 times a day, for 4 weeks. After treatment, an 8-week follow-up will be conducted. XFZY oral liquid will be manufactured in strict accordance with the standards of the Chinese Pharmacopoeia (2015) [30], and the process strictly abides by the Good Manufacturing Practice (GMP). XFZY will be manufactured by Jilin Aodong Pharmaceutical Group Co., Ltd., in line with the requirements of GMP.

#### 2.5.2. Placebo Group

Placebo was selected as the comparator to assess the efficacy of XFZY owing to substantial placebo effect in the treatment of headache [31]. Participants in the placebo group will also be given 20 ml of the placebo, 3 times a day for 4 weeks. The follow-up period is the same as that of the experimental group. The placebo is made from honey, white granulated sugar, fried brown sugar, bitterant, natural edible pigments, food antiseptic, and thimbleful ginseng essence, to mimic the flavor of Chinese herbs. It also meets the hygiene inspection requirements. The placebo will also be provided by Jilin Aodong Pharmaceutical Group Co., Ltd., in line with the requirements of GMP.

